### Randomization and Masking

This study will use a computer-generated random list obtained from Random Allocation Software [47] to randomize groups using a simple randomization technique by 2 biostatisticians (1 for each country) who are not part of the research team to ensure assignment concealment. Each country’s research team is expected to have 59 research subjects in the treatment group and 59 research subjects in the control group, totaling 118 adolescent girl participants from each country. The group randomization process will be concealed from the study subjects. Thereafter, the researchers will notify subjects of their group membership through invitations to participate in the treatment intervention or usual care sessions.

### Treatment Activities and Procedures

This research will be reported in line with the guidelines for the Consolidated Standards of Reporting Trials (CONSORT) [48]. The study was registered in a clinical trials registry before the recruitment of the first participant. A 16-session CBT manual incorporating web-based counseling techniques and principles and local wisdom approaches to the treatment of GAD among adolescent college girls with FGID symptoms will be developed by the research team for this study. The research team will adapt evidence-based techniques and procedures from existing CBT intervention manuals for GAD and FGID treatments with a focus on cultural components, traditions and values, and local wisdom, as well as web-based counseling techniques and processes, to address GAD and FGID symptoms among adolescent college girls. Each web-based session for the treatment group as well as the usual care session for the control group in each country (study site) is expected to last for 90 minutes each, once a week for 4 months. To assess the efficacy of CBT combined with local wisdom and web-based counseling approaches, we used the usual care as a comparison group. This study defines usual care as whichever treatment for GAD and FGIDs adolescents receive from their regular health care providers or therapists. This form of comparison group was selected to appraise the effects of CBT combined with local wisdom and web-based counseling approaches against the treatments that would normally be available without this intervention. The use of usual care as a comparison group also contributes to the viability of the trial since other clinicians are not required to be trained in a particular approach to comparator therapy. Due to this study’s design, it is possible to compare the effects of CBT combined with local wisdom and web-based counseling methods with the usual practice in GAD treatment for adolescent girls with FGIDs. Three specialist raters in each country will evaluate the treatment’s integrity. During the project, 2 postgraduate-level psychologists with a master’s degree will serve as research assistants in each country. Two cognitive behavioral therapists with a doctorate in counseling psychology will provide the web-based CBT intervention for the treatment group, while the usual care intervention for the control group in each country will be provided by 2 CBT practitioners with doctorate degrees in psychology. The recruitment process will begin in July 2023, and the trial will begin in August 2023. The posttest assessment data gathering will be undertaken by November 2023. A summary of the treatment intervention is shown in Table 1.

**Table 1 table1:** Summary of the intervention components.

Sessions	Integrated web-based counseling with local wisdom CBT^a^
Initial assessment (session 1)	In the first session, the counselor and clients will engage in an initial assessment to identify the presenting issues and set goals for therapy. This assessment typically takes 1 session. This stage involve the use of a web-based assessment system.
Sessions 2-3	Psychoeducation (2 sessions): Over 2 sessions, the counselor provides educational materials and resources to the clients through text, videos, or web-based sources. The counselor explains the concepts of CBT, the connection between thoughts, feelings, and behaviors, and introduces the techniques and strategies that will be used in therapy.
Sessions 4-5	Identification of negative thought patterns (2 sessions): This process involves self-observation, reflection, and discussion, taking into account the perspective of cultural values and local wisdom. By incorporating cultural perspectives and values, the counselor aims to create a culturally sensitive and inclusive environment that respects the clients’ cultural background. The exploration and identification of these patterns typically take 2 sessions, allowing sufficient time for the client to reflect and discuss their experiences within the context of their cultural beliefs and values.
Sessions 6-9	Restructuring negative thoughts (4 sessions): Once negative thought patterns are identified, the counselor and clients collaborate to restructure these thoughts and replace them with more realistic, balanced, and positive thoughts, integrating the principle of “nature as the master teacher” from Minangkabau culture in Indonesia. This process involves techniques such as realistic thinking, thought replacement, and asking challenging questions while drawing inspiration from nature’s wisdom. By incorporating local wisdom, the counselor helps the clients develop a deeper understanding and connection with their cultural roots. In this respect, the Ubuntu counseling model as a local wisdom approach will be integrated to assist the South African adolescents during the treatment sessions since it involves integrating African culture into the therapeutic process in that it recognizes the relevance of culture to patient mental health and self-identity. Several group processes are emphasized in the Ubuntu counseling model, including communality, cooperation, and oneness among others. Several traditions and values are also intrinsic to the Ubuntu counseling model, and they determine how mental disorders are understood and treated in South Africa.
Sessions 10-13	Development of coping skills (4 sessions): The counselor assists the clients in developing healthier coping skills. This includes stress management strategies, relaxation techniques, problem-solving skills, and fostering adaptive thinking patterns. It typically takes 4 sessions to introduce and practice these skills.
Sessions 14-15	Assignments and exercises (2 sessions): Throughout therapy, the counselor assigns tasks and exercises for the clients to apply the concepts and skills learned in sessions to their daily lives. The counselor may review progress and provide feedback in 2 dedicated sessions for discussing and reviewing assignments.
Session 16	Monitoring and feedback (1 session): The counselor uses web-based monitoring tools, such as questionnaires or web-based daily journals, to track changes in the clients’ thoughts, feelings, and behaviors. In 1 session, the counselor provides constructive feedback based on the information gathered and the progress made.

^a^CBT: cognitive behavioral therapy.

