## Methods

### Research Design

This study is developmental research involving the systematic and conceptual design of a psychological treatment approach. The development model that will be used as the basis for this research activity is one adapted from the ADDIE (Analysis, Design, Development, Implementation, and Evaluation) model [42,43]. A prospective, parallel randomized controlled trial design involving pre- and posttesting of a treatment group and a control group will be used by the researchers [44]. At the end of a diagnostic interview conducted by the researchers, participants who are considered eligible for the study will be randomly assigned to 1 of 2 groups: the web-based CBT group or the usual care control group.

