### Research Subjects

The research subjects will consist of female adolescent students in Indonesia and South Africa (aged 15-17 years); 118 people from each country will be recruited from general practice or family medicine clinics as well as high schools within each study area to arrive at an overall sample of 236 participants for this study. An initial assessment will be conducted on 1000 potential participants (500 adolescent girls per country), who will be screened according to the research criteria so that a representative sample for the intervention may be obtained. The results of a recent study [45] found that 44.1% of participants were able to complete a CBT program using a web-based approach and that the average completion rate for the 12 sessions was 7.8 (65%). Therefore, we will take into account the attrition rate of 55.9% by including 55.9% extra participants in our initial sample for each group produced by the G*power (Heinrich-Heine-Universität Düsseldorf) sampling program [46]. To account for the potential effects of missed sessions in a standard web-based CBT program, as shown by recent research [45], 4.2 sessions (35%) will be added to the 12-session program, which will result in approximately 16 sessions (to be delivered over 4 months). Based on the G*power calculation, the required sample size is 38 participants per group (85% statistical power; medium effect size Cohen *d*=0.5; a priori probability level of 0.5) for a linear mixed model (LMM) analysis. Given the presumed attrition rate, we will recruit 59 participants per group in each country.

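### The control arm is defined as care from each participant's own providers but scheduled as weekly sessions by trial-supplied CBT practitioners; if those sessions run, the claimed comparison with usual practice does not follow

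*Protocol article*

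**What the plan says.** All the main statements are in Treatment Activities and Procedures in the protocol article.

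- **Definition.** "This study defines usual care as whichever treatment for GAD and FGIDs adolescents receive from their regular health care providers or therapists".
- **Purpose.** This comparator was chosen to judge the package "against the treatments that would normally be available without this intervention", and the section concludes that the design permits a comparison "with the usual practice in GAD treatment for adolescent girls with FGIDs".
- **Dose.** One sentence sets the schedule for both arms. Its wording for controls is: "session for the control group in each country (study site) is expected to last for 90 minutes each, once a week for 4 months".
- **Deliverers.** "the usual care intervention for the control group in each country will be provided by 2 CBT practitioners with doctorate degrees in psychology".
- **Training.** A stated advantage of usual care is that "other clinicians are not required to be trained in a particular approach to comparator therapy".

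Other sections bear on the same point. Research Design names the arms as "the web-based CBT group or the usual care control group". Randomization and Masking has the researchers invite controls to sessions of usual care, and puts 59 participants in each arm in each country. Inclusion and Exclusion Criteria requires willingness to attend a usual care programme. Data Analyses counts as a complier anyone who attended at least 80% of the programme sessions, and refers to compliers in both arms.

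**The concern.** Care from a girl's own doctor or therapist has no weekly dose fixed by the trial and no deliverers named by the trial. The control arm as scheduled has both. The two descriptions answer different questions. Against regular-provider care, the trial estimates what the package adds to or changes from care already available. Against scheduled sessions, it estimates how the package differs from another practitioner-led programme with similar scheduled contact.

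The stated inference holds under only the first. If the sessions are delivered, a null result could not be read as showing the package to be no better than usual practice. A positive result would not measure the gain over what is normally available. Two country teams working from the same text could also set up different control arms in good faith.

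**Working it through.** No figure in the plan needs reproducing. The check is a comparison of statements, with simple arithmetic on dose and staffing.

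**1. Who delivers control care?** The definition says the participants' regular providers. The staffing sentence says 2 CBT practitioners per country. Could these be the same people? Controls per country: 59 (Randomization and Masking). Practitioners: 2. So 59 / 2 = 29.5, or about 30 controls each. Participants are "recruited from general practice or family medicine clinics as well as high schools within each study area". It is not plausible that two people are already the regular providers of about 59 girls drawn from such a mix of sources.

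**2. At what dose?** The definition fixes none. The schedule gives 90 minutes weekly for 4 months. Research Subjects puts the treatment programme at approximately 16 sessions over 4 months, and Table 1 lists 16. The session count is not stated separately for controls. It is inferred from the shared sentence:

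- scheduled time per treated participant: 16 × 1.5 h = 24 h
- scheduled time per control participant, same schedule: 16 × 1.5 h = 24 h

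**3. Which description does the rest of the article support?**

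| Section | Own-provider care | Trial-run sessions |
|---|---|---|
| Treatment Activities and Procedures: definition and purpose | yes | no |
| Treatment Activities and Procedures: schedule and deliverers | no | yes |
| Randomization and Masking: invitation to sessions | no | yes |
| Inclusion and Exclusion Criteria: willingness to attend a programme | no | yes |
| Data Analyses: compliers in the control arm, by sessions attended | no | fits |

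If controls only see their own providers, the 80% attendance rule has no evident denominator in that arm.

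**4. Does the inference follow?** If controls receive only regular-provider care, the usual-practice claim stands, but the schedule and staffing text are wrong. If the sessions are delivered, that text is right and the claim does not follow. No reading leaves the whole section correct.

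**The case against.** The strongest reply is that the section is loosely worded and does not describe two rival designs. The remark that no comparator training is needed may mean that the practitioners give their ordinary, unscripted care. The definition would then describe content and the staffing sentence delivery, with the detail left to a fuller protocol. Part of this stands: what happens inside the control sessions is detail an article may omit, and its absence is not the complaint. But the reading does not explain why the trial supplies deliverers when the definition says regular providers give the care, nor where the weekly dose comes from. Condensing explains omissions. It does not explain two incompatible statements.

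A second reply is that the randomised comparison, the outcomes and the linear mixed model remain valid either way. That is correct. What changes is the question answered and the conclusion that can be drawn.

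A third is that concurrent care is already acknowledged. Primary Findings asks participants, without restriction by arm, to disclose treatments and report changes in medication dose, and lists concurrent treatment as a limitation. That is fair, and silence on background care is not counted here as an error.

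A reader might infer more than the article supports:

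- **That controls receive CBT.** The deliverers are CBT practitioners, but the content of their sessions is not stated.
- **That excluding girls currently in CBT proves the practitioners cannot be their regular providers.** The criterion restricts the treatment a girl is receiving, not her therapist's qualification. Only the staffing ratio and the recruitment sources bear on this.
- **That the two readings differ by 24 hours of care between arms.** This would count trial contact only and leave out regular-provider contact, which is the comparator under the definition.

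**Conclusion.** Treatment Activities and Procedures contradicts itself on who delivers control care and at what dose, and no other section reconciles the two. If the scheduled sessions are delivered, the comparator is a practitioner-led programme of similar scheduled contact (about 24 h in each arm), and the claim to compare with normally available care or usual practice does not follow.

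This rests on two assumptions: that the shared schedule sentence applies to controls as written, and that weekly sessions for 4 months mean about 16, as in the treatment programme.

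A reader might go on to infer a biased estimate or a specific loss of power. The article does not support either. Without the content of the control sessions, the direction and size of any change in the treatment effect cannot be determined, and any power figure would rest on an assumed dilution that the article does not give.

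**What to change.** Before the first randomisation, state one control condition for both countries: who delivers it and at what dose. The choice is for the investigators.

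**If the sessions are kept:**
- In Treatment Activities and Procedures, remove the claims about normally available care and usual practice, and describe regular-provider care as background care in both arms.
- Relabel the control group in Research Design.
- Word the trial's conclusions as a comparison with practitioner-led sessions of similar duration.

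**If true usual care is meant:**
- In Treatment Activities and Procedures, delete the control session schedule and the sentence assigning CBT practitioners to the control arm.
- Align the invitation wording in Randomization and Masking and the willingness criterion in Inclusion and Exclusion Criteria.
- In Data Analyses, define compliance (80% of programme sessions) on treatment-arm sessions only, and specify the complier-adjusted causal effect so that it no longer relies on observed attendance in the control arm.

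The cost is wording changes across Research Design, Randomization and Masking, Treatment Activities and Procedures, and Inclusion and Exclusion Criteria, depending on the option. The second option also needs a revised complier analysis in Data Analyses. The randomisation method and outcome measures are unaffected.

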### Inclusion and Exclusion Criteria

To be considered eligible, participants must (1) be between the ages of 15 and 17 years, (2) be experiencing moderate to severe GAD and FGID symptoms at baseline, (3) speak and understand English to a reasonable level, (4) be willing to take part in the web-based CBT program or attend the usual care program, (5) have been taking continuous doses of anxiety medications for at least two months before the commencement of the program, (6) have a smartphone or tablet device that is capable of running Whatsapp, Zoom, or the Konselo counseling app and have access to the internet, which is necessary to participate in the program sessions, and (7) demonstrate the ability to commit to the expectations of the trial. Some conditions will exclude participants from the study. This includes (1) participants who cannot answer questions in the assessment tools on their own with a reasonable degree of English, (2) participants affected by psychiatric or medical comorbidities that would severely impact their ability to participate or adhere to the program schedule, (3) persons who are currently receiving CBT treatment, (4) individuals who have practiced meditation regularly or previously, (5) a lack of internet access or the inability to use a device that is capable of connecting to the internet, and (6) inability to commit to the expectations of the trial. In each country, 2 postgraduate-level research assistants with a master’s degree in psychology will be trained to screen prospective participants using these inclusion and exclusion criteria by telephone. On completion of the screening process and after it has been determined that participants are eligible for the study, they will be invited to complete a diagnostic interview with the research investigators in each study area to additionally validate their eligibility for the study. Participants will be reached by phone in line with the schedule of the program as soon as it has been determined that they are eligible to participate in the research study.

### Outcome Measures

Questionnaires that will be used in this study include the Functional Gastrointestinal Disorder Checklist (FGI-Checklist) [49] to collect data related to FGIDs and the Generalized Anxiety Disorder 7-item (GAD-7) screening tool [50] to measure the anxiety conditions experienced by respondents.

The FGI-Checklist includes the 20 most common FGID symptoms, which encompass a series of symptoms across the GI tract [49]. Five subscales contribute to the total score of the FGI-Checklist, including abdominal and bowel syndrome (7 items; Cronbach α=.86), functional dyspepsia syndrome (5 items; Cronbach α=.87), reflux syndrome (4 items; Cronbach α=.80), esophageal syndrome (3 items; Cronbach α=.69), and nausea and vomiting syndrome (2 items; Cronbach α=.73). Several single items on the FGI-Checklist are used to ascertain the severity of global dyspeptic symptoms, abdominal symptoms, stool frequency, and stool form as per the Bristol stool scale. Thus, it is often seen as a comprehensive symptom assessment scale covering esophageal, epigastric, and abdominal symptoms. It is a self-administered outcome measure with a 7-day recall period [49]. Patients are required to rate the intensity of each symptom using 4 response options to indicate impairment in daily activities due to the symptom as follows: 0=none, 1=mild (not affecting daily activity), 2=moderate (some daily activities are affected), and 3=severe (almost all daily activities are affected). The FGI-Checklist total score, which ranges from 0 to 3, is calculated by averaging the scores of the 20 items. Patients with mild (monthly) to severe (weekly) symptoms can be identified with the FGI-Checklist. A higher score represents more severe symptoms [49].

It has been demonstrated that the GAD-7’s internal consistency is excellent (Cronbach α=.92) and its test-retest reliability is adequate (intraclass correlation=0.83) [50]. The GAD-7 has a 4-point response scale ranging from 0 (not at all) to 3 (nearly every day). Scores between 0 and 4 indicate minimal GAD, 5 to 9 indicate mild GAD, 10 to 14 indicate moderate GAD, and 15 to 21 indicate severe GAD [50]. The GAD-7 also has a strong correlation with patients’ mental health (*r*=0.75), social functioning (*r*=0.46), general perceptions of health (*r*=0.44), bodily pain (*r*=0.36), role functioning (*r*=0.33), and physical functioning (*r*=0.30) [50]. An invaluable feature of the GAD-7 is its ability to assess changes in anxiety symptoms severity over recent weeks (that is, over the previous 2 weeks).

### Data Analyses

The analyses of the data in this study will include descriptive analysis, analysis of the coefficient of agreement between program raters (interrater reliability), and internal consistency analysis using Cronbach α and partial η^2^ (effect size statistics). A sensitivity analysis will also be carried out to avert potential data dredging. The Mauchly sphericity test and Levene equality of variance test will be carried out to ensure that the assumptions of the chosen statistical test are met. LMM will be used to analyze the primary outcome measures statistically based on the principle of intention-to-treat to determine whether considerable changes have occurred over time [51]. By using LMM, participants with incomplete data will be included in the analyses so that treatment effects can be assessed over time (group time interaction) [51]. Using LMM, the treatment group, time, and interactions between the treatment group and time will be considered fixed factors; the covariance structure will be constructed in an unstructured manner. We will ascertain posttest outcomes in terms of mean changes in GAD-7 and FGI-Checklist scores from baseline to 4 months following the pretest. Complier-adjusted causal effect (CACE) analysis will be conducted based on the causal framework and estimation methods to account for variations in treatment effect due to variations in treatment adherence between the groups [51,52]. We will calculate CACE as the difference between the mean GAD-7 and FGI-Checklist scores of compliers in the treatment group as well as the control group. To be considered a complier, a participant must have attended 80% or more of the program sessions, which is a frequently used threshold [51,53]. A bootstrapping technique will be used to determine standard errors. Statistical analyses will be completed using R (R Core Team) to analyze the CACE data and SPSS (version 29; IBM Corp) for the rest of the analyses. *P* values of .05 or less will be considered statistically significant.

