This study hypothesizes that there will be significant mean changes in GAD scores and FGID scores after exposure to this combined approach of CBT, web-based counseling, and local wisdom in the Indonesian and South African populations. So far, pharmacotherapy and psychological interventions have undertaken the management of anxiety that results in FGIDs, and vice versa [25,28]. These psychological interventions include psychotherapy, psychodrama, CBT, relaxation therapy, and hypnosis [33-36]. Psychological intervention refers to psychotherapeutic methods designed to change a person’s cognition, perception, or behavior. Psychodynamic psychotherapy focuses on how maladaptive thoughts and behaviors occur [35,36]. The psychodynamics of interpersonal psychotherapy are more concerned with the relationship between therapist and patient. This method emphasizes that the therapist and patient form a robust, cooperative working alliance. Meanwhile, CBT aims to improve the quality of life by changing the patient’s thoughts or patterns of thinking and behavior. Relaxation therapy allows the patient to experience the physical and mental pleasure that relaxation brings to correct the psychological and physiological dysfunction caused by tension [12,37,38]. Hypnotherapy is the use of hypnosis to treat patients and improve their condition. For this reason, it is necessary to have a new approach that uses collaborative and cross-approach concepts to get more effective and efficient results. Following previous research, there are empirical results regarding the impact of psychological interventions on reducing anxiety symptoms and improving pain due to FGID; there is still no single fixed model with a combination of approaches to reduce anxiety conditions effectively. In addition, existing research has not shown an in-depth evaluation process of research results in the adolescent population. This study uses a CBT approach that has proven useful for clients with maladaptive disorders such as stress and anxiety. The study also uses the web-based counseling intervention approach as a way to evaluate and supervise the progress of counseling and also uses the implementation of local wisdom. The therapeutic model of local wisdom is added to this study, considering that behavioral change is closely related to the cultural values it carries [39-41]. In this respect, the Ubuntu counseling model as a local wisdom approach will be integrated to assist the South African adolescents during the treatment sessions since it involves integrating African culture into the therapeutic process in that it recognizes the relevance of culture to patient mental health and self-identity [58]. This study uses cross-cultural analysis with very different cultures, namely Indonesian and South African cultures. The cross-cultural analysis will show whether the intervention can be applied to 2 different cultures with almost the same indications of anxiety in terms of symptoms and aggravating factors. The results of this study will contribute to the literature on GAD and FGID treatment by informing clinicians about the potential benefits of CBT combined with local wisdom and web-based counseling approaches for adolescent girls with FGIDs experiencing GAD. However, in this study, there are some potential limitations, including that the treatment pattern does not allow for the blinding of therapists, the possibility that participants may use other interventions or treatments while taking part in the study, and a sample size that may make it impossible to generalize the study results to a larger population and spot subtler effects. While participating in the trial, participants will be required to speak frankly about their medications and treatments. In addition, they will be required to notify the researchers about any modifications to their medication doses throughout the study. In this way, the results can be taken into account with respect to any confounding variables.

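### The stated mixed model has no country term, so it cannot supply the cross-cultural comparison that the article announces

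*Protocol article*

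**What the plan says.** The Data Analyses section of the protocol article names the fixed part of the model explicitly: "the treatment group, time, and interactions between the treatment group and time will be considered fixed factors". It adds that "the covariance structure will be constructed in an unstructured manner". Country is not mentioned in that section as a fixed or random effect, a stratum, a subgroup, an interaction or a reason to fit separate models.

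Elsewhere country is part of the design:

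- Randomization and Masking: the lists are handled "by 2 biostatisticians (1 for each country) who are not part of the research team", and each country expects "59 research subjects in the treatment group and 59 research subjects in the control group".
- Research Subjects: the sample size is set per group in each country, 59 per group, 236 in total.
- Table 1, sessions 6-9: the restructuring work uses a principle "from Minangkabau culture in Indonesia", whereas "the Ubuntu counseling model as a local wisdom approach will be integrated to assist the South African adolescents during the treatment sessions".
- Treatment Activities and Procedures: the comparator is whatever care participants receive from their regular providers, so it may differ by country.

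The Discussion (Primary Findings) then states: "This study uses cross-cultural analysis with very different cultures, namely Indonesian and South African cultures", and "The cross-cultural analysis will show whether the intervention can be applied to 2 different cultures". It gives no method for this.

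**The concern.** The model as listed and the conclusion as announced do not fit together. A model with group, time and group x time has no parameter for a difference in treatment effect between countries. The mismatch can be resolved in two ways, and each leaves something out.

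If all 236 participants are pooled, differences between countries in change over the 4 months go into the residual, and the stratum within which participants were allocated is ignored. If the model is run once per country, the strata are respected, but the output is two unconnected results. A reader would then tend to set one p-value against the other, and that is not a test of whether the effects agree. With samples of this size, one significant and one non-significant result can arise by chance from the same true effect, and could be read as the intervention working in only one culture.

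Leaving pooled or per-country analysis open also allows the choice to be made after the data are seen. The section's own sensitivity analysis is meant to guard against that kind of data dredging.

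**Working it through.** **Inputs from the article.** 59 per arm in each country (38 x 1.559 = 59.2, the article's own attrition allowance); effect size d = 0.5; significance at 0.05. The article gives no figure for a country contrast, so there is none to reproduce. Whether 38 is itself right is a separate matter and is not needed here.

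**Assumptions.** Two-sided testing (the article does not state sidedness). Outcome SD = 1. Identical true effect of 0.5 SD in both countries. Baseline-post correlation r between 0.5 and 0.7, which the article does not give. Residual variance v = 1 for post scores alone, 2(1 - r) for change scores and 1 - r^2 with baseline as covariate.

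**Formulas.** With n per arm in each country:

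- Per-country power p: two-sample t-test with non-centrality (0.5/sqrt(v)) x sqrt(n/2).
- Probability that exactly one of two independent tests is significant: 2p(1 - p).
- SE of the difference between the two country effects: sqrt(4v/n). The 95% half-width is 1.96 x SE.

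**Results at n = 59.**

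| Analysis | v | Power per country | Tests disagree | 95% half-width (SD) |
|---|---|---|---|---|
| Post scores, or change at r = 0.5 | 1.00 | 76.8% | 36% | 0.51 |
| Baseline as covariate, r = 0.5 | 0.75 | 87.5% | 22% | 0.44 |
| Change, r = 0.7 | 0.60 | 93.5% | 12% | 0.40 |
| Baseline as covariate, r = 0.7 | 0.51 | 96.5% | 7% | 0.36 |

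First row in full: 2 x 0.768 x 0.232 = 0.356; SE = sqrt(4/59) = 0.260; 1.96 x 0.260 = 0.51.

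**If outcome data are lost.** As an illustration only, take 26 per arm (59 x 0.441 = 26.0, from the programme-completion rate in Research Subjects). Over the same four analyses, disagreement is 42% to 50% and the half-width 0.55 to 0.77 SD. Completing the programme is not the same as supplying outcome data, and the mixed model keeps incomplete cases, so 26 is a pessimistic case and not a forecast.

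**Power for a country contrast.** For an assumed between-country difference of 0.5 SD, power is Phi(0.5/SE - 1.96). At 59 per cell this is 48% with v = 1 and about 77% with v = 0.51. With v = 1, about 144 per cell would be needed for 85%.

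**Cost of pooling without country.** Suppose the countries differ by D in the analysed outcome, with D assumed to be 0.5 to 1.0 SD and v = 1. The SD rises by the factor sqrt(1 + D^2/4), that is 1.03 to 1.12. Pooled power for d = 0.5 falls from 97% to 96-93% at 118 per arm, and from 87% to 85-79% at 76 per arm (2 x 38).

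**The case against.** Several points can fairly be made on the other side.

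*Full detail may sit elsewhere.* A journal article condenses, and stratification covariates and interactions are often left to a fuller document. This would carry weight if the article had only said that a mixed model would be used. It lists the fixed factors and, in the same text, announces a conclusion that those factors cannot deliver. The mismatch is therefore on the page.

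*The model may be meant per country.* This stands as a possible reading: the sample size is set within each country and the hypothesis names both populations. A reader might infer that the plan fails to account for the stratum either way. That is not supported, because a model fitted separately in each country conditions on country fully. What is missing under that reading is only the comparison.

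*Applicability in two cultures need not mean equal effects.* This also stands in part. The announced question could be answered by an effect with its interval in each country. The article never says it will compare two p-values; that risk arises because nothing else is specified.

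*Omitting country does not bias the pooled effect.* Correct in expectation under the planned 1:1 allocation in each country. Simple randomisation does not guarantee 59:59: the arm count among 118 has SD sqrt(118 x 0.25) = 5.4. Adjusting for country deals with such chance imbalance, but this is not evidence of systematic bias.

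*Separate lists are not stated.* One biostatistician per country makes them likely, but the article mentions a computer-generated list without saying there are two. The point does not depend on it.

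**Conclusion.** The point holds as a mismatch between the stated model and the announced conclusion. It does not show that the treatment estimate is invalid. Pooled, the listed model loses modest precision; fitted by country, it gives no between-country comparison. On the assumptions above, separate tests of an identical effect at 59 per arm would disagree with probability of about 7% to 36%, and the between-country difference would be known to within about 0.36 to 0.51 SD either way. A reader might take the upper ends, or the 26-per-arm figures, as the expected result. The documents do not support that, because they give no baseline-post correlation and retain incomplete cases.

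Adding the country contrast will not turn the trial into a test of consistency. An interval nearly as wide as the planned effect itself (0.5 SD) cannot show that the effect is the same in both cultures, and a non-significant interaction should not be read that way.

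**What to change.** 1. Fit one model on all 236 participants with group, time, group x time, country and country x time, and state that the primary estimate is the between-group difference in change to 4 months averaged over the two countries.
2. Pre-specify a second model that allows the group x time effect to differ by country (group x time x country and its lower-order terms). Report the effect in each country and the difference between them, each with a 95% CI.
3. Base the cross-cultural statement in the Discussion on that difference and its interval, and describe it as exploratory and imprecise.

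Country is known for every participant, so no extra data or recruitment is needed; the change is to the analysis wording and should be made before outcomes are seen. If separate per-country analyses were intended, the averaged primary estimate is a real change of target. The article should then say so and state how it relates to the per-country sample size. The per-country effects remain available from the second model.
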